#### Genomic relatedness

We expect a maximum of 10% (95% CI 6.3–13.7%) of 250 community diagnosed Index TB cases will have an *Mtb* isolate that is genomically ‘identical’ to another Index case, compared to approximately 60% of Index TB case/household contact TB case pairs. Percentages for Index case/neighbourhood case pairs will lie between these values. Assuming we identify 35 culture-positive cases in contacts in 250 households and 75 culture-positive cases in neighbourhoods, we will have >95% power to detect significant differences (p = 0.05 level of significance), in percent genomically ‘identical’, for comparisons between community and Index TB case/household TB case pairs and between community and Index TB case/neighbourhood case pairs. We will also have over 80% power to detect a significant difference for a household versus neighbourhood comparison, if 60% or more of Index case/household case pairs are genomically ‘identical’ and 30% or less of Index case/neighbourhood case pairs are genomically ‘identical’.

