#### 2) Whole-genome sequencing and social network analysis

From each household contact who is diagnosed with TB, as well as Index cases, an interview will be undertaken using a social network questionnaire, and sputum cultured for Mtb will undergo WGS to ‘fine map’ their relatedness [19]. We will use the BWA-MEM algorithm to map the sequence data to the H37Rv reference genome. Variants will be called using Pilon (v1.22). We will assign a call as missing if the valid depth at a specific site is less than 12, if the mean read mapping quality at the site does not reach seven, or if none of the alternative alleles account for at least 85% of the valid coverage.

Pairwise genetic distances between each TB patient will be determined, after removing single-nucleotide polymorphisms (SNPs) in highly repetitive genes such as the PE/PPE genes and loci under strong selection. [20, 21]. For all pairs, we will obtain the shortest travel time between two points as an approximation of the geographic distance using Open Source Routing Machine, a publicly available tool that analyses Open Street Map road network data. We will assess the relationship between geographic and genetic distance across all pairwise samples to determine the relative contribution of close versus distant contacts in TB transmission. For five definitions of SNPs distances (0–1, 2–3, 4–5, 6–10, and 11–30 SNPs different), we will first compare the odds of genetic relatedness at each of the five levels among pairs within the household, pairs within the neighbourhood, and pairs from different neighbourhoods. We will repeat the same but classifying the pairs in to five categories (within the household, 0–5, 5–10, 10–20, and 20 or more minutes of travel time apart). We will also determine whether any of the household contacts share common meeting places such as employment venues, places of worship, markets, or restaurants.

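### The planning interval of 6.3–13.7% treats 250 Index cases as independent, but matching between Index cases is mutual, so it is too narrow by a factor of about 1.4 if matches are mostly pairs and by more if sets are larger

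*Protocol article*

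**What the plan says.** The Genomic relatedness part of the sample size section sets a reference value for the community, given as "We expect a maximum of 10% (95% CI 6.3–13.7%) of 250 community diagnosed Index TB cases will have an"; the event counted is an "isolate that is genomically ‘identical’ to another Index case". It expects about 60% for Index/household contact pairs, and a value between these two for Index/neighbourhood pairs.

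The power statement reads "we will have >95% power to detect significant differences". The case numbers behind it are given as "Assuming we identify 35 culture-positive cases in contacts in 250 households and 75 culture-positive cases in neighbourhoods", the threshold as "p = 0.05 level of significance", and it is made "for comparisons between community and Index TB case/household TB case pairs and between community and Index TB case/neighbourhood case pairs". No neighbourhood percentage is attached to this statement. The figure of 30% or less appears only in the next sentence, for household versus neighbourhood.

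The section on whole-genome sequencing and social network analysis says how relatedness is measured: "Pairwise genetic distances between each TB patient will be determined". The article mentions no design effect and no expected size of matching sets.

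**The concern.** A binomial interval with n = 250 requires each Index case to be matched or unmatched independently of the others. The outcome rules this out. Genetic distance between two patients is symmetric, so one Index case cannot match another without that other also counting as matched. Exactly one matched case among the 250 is impossible. The 25 expected matched cases form at most 12 sets (11 pairs and one triple), and fewer if sets are larger. The dependence follows from the definition and needs no assumption about correlation.

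At stake is the stated precision of the percentage that serves as reference in two of the three planned genomic comparisons. The Discussion links the rate of genomic matching to the choice between active case finding and preventive treatment.

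**Working it through.** **Inputs from the article.** p = 0.10 and n = 250 Index cases; 75 neighbourhood and 35 household culture-positive cases; significance level 0.05. **Assumed:** two-sided tests, pooled z-test with normal approximation, contact pairs independent of each other, and the size m of matching sets, which the article does not give.

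**1. Reproduce the printed interval.** SE = sqrt(0.10 × 0.90 / 250) = 1.897%. Then 10% ± 1.96 × 1.897% = 6.28% to 13.72%, which rounds to the printed limits. Other common methods do not fit:

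| Method | 95% limits |
|---|---|
| Wilson | 6.9–14.3% |
| Clopper-Pearson | 6.6–14.4% |
| Agresti-Coull | 6.8–14.4% |
| Jeffreys | 6.7–14.2% |
| Wald with continuity correction | 6.1–13.9% |

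**2. Allow for mutual matching, pairs only (m = 2).** Three approximations:

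- *Effective sample size.* n/m = 125. SE = sqrt(0.09/125) = 2.68%; interval 4.7–15.3%; width factor sqrt(2) = 1.41.
- *Ratio estimator, with each pair or unmatched case as a unit.* The share of units that are pairs is q = 0.10/(2 − 0.10) = 0.0526. Mean unit size is 1.0526, giving 250/1.0526 = 237.5 units. Variance = [(1 − q) × 0.10² + q × 2² × 0.90²] / (237.5 × 1.0526²) = 0.180/263.2 = 0.000684. SE = 2.62%; interval 4.9–15.1%; factor 1.38.
- *Poisson number of pairs.* The expected number is 25/2, so SE = 2 × sqrt(12.5)/250 = 2.83%; interval 4.5–15.5%; factor 1.49.

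A simulation of 250 draws from 2,364 equally common strains, which gives about 10% matched and nearly all in pairs, had a variance about 1.87 times binomial (factor 1.37). The nominal 95% Wald interval covered the expected percentage about 83% of the time.

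**3. Larger sets.** With all sets of three, the effective n is about 83, SE = sqrt(0.09/83) = 3.29%, and the interval is about 3.5–16.5%. The other two approximations give 3.8–16.2% and 3.2–16.8%, so the factor is 1.67 to 1.83. An assumed mix of sets of 2, 3, 4 and 5 (70/15/10/5%) gives a factor of about 1.6.

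**4. Effect on power.** Power = Φ[(d − 1.96 × s0)/s1], where d is the difference, s0 the pooled SE and s1 the unpooled SE. Example for 10% versus 30% at effective n = 125: the pooled proportion is (12.5 + 22.5)/200 = 0.175, s0 = 0.0555, s1 = 0.0593, and (0.20 − 0.1088)/0.0593 = 1.54, so power is 93.8%.

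| Community 10% versus | n = 250 (independent) | Effective n = 125 (pairs) | Effective n = 83 (triples) |
|---|---|---|---|
| Neighbourhood 30% (n = 75) | 97.4% | 93.8% | 89.0% |
| Neighbourhood 31% (n = 75) | 98.2% | 95.3% | 91.3% |
| Neighbourhood 35% (n = 75) | 99.6% | 98.7% | 97.0% |
| Household 60% (n = 35) | >99.9% | >99.9% | >99.9% |

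**5. Effect on the test.** In the simulation of step 2, with both true percentages at 10%, an ordinary pooled z-test rejected about 7% of the time against a nominal 5%.

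**The case against.** The other side has several sound points.

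- *Nothing is miscalculated.* The printed limits reproduce exactly. What is wrong is the independence assumption behind the formula. That stands, but the limits still do not describe the precision of the stated quantity.
- *A reader might infer that the claim of more than 95% power is false.* The article does not support that. It names no neighbourhood percentage for this comparison, and 30% belongs to another one. With pairs, one percentage point more (31%) brings power back above 95%. The 10% is also called a maximum: at effective n = 125 against 30%, power is 96.0% if the true community value is 9% and 97.5% if it is 8%.
- *A reader might infer that the final interval will under-cover and the final test will reject too often.* No variance method or test is fixed for the Index-to-Index percentage, and such detail may sit in a full protocol or analysis plan that is not shown. The 83% coverage and 7% rejection apply only if the planning formula is carried into the analysis.
- *The replacement interval rests on assumed set sizes.* This is correct. Nor is 1.4 a strict floor, since the models for pairs start at 1.37. Any restated interval must carry its assumption.

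None of this rescues 6.3–13.7%, because no set structure makes mutually matched cases independent.

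**Conclusion.** The point holds as a correction to a planning figure. The printed interval uses the variance for 250 independent cases, whereas matched Index cases can occur only in sets of two or more. It is too narrow by a factor of about 1.4 if nearly all sets are pairs (1.37 to 1.49 across models), and by about 1.7 to 1.8 if all are triples. The direction follows from the definition of the outcome; the size depends on set sizes that the article does not give.

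The consequence is modest. Community versus household keeps more than 99.9% power. Household versus neighbourhood and the planned odds analysis by SNP band are not touched by this point. Only community versus neighbourhood loses some power, about 4 points with pairs at an assumed 30%, with contact pairs treated as independent. The key outcomes, prevalence and incidence, are unaffected.

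**What to change.** - Restate the planning interval as roughly 4.5–15.5% (about 4.7–15.3% at an effective n of 125), labelled as assuming that matched Index cases occur in pairs and as wider for larger genomic clusters, for example about 3.5–16.5% for sets of three.
- Restate the community-versus-neighbourhood power with this variance and name the neighbourhood percentage assumed. At 30% it is about 94% with pairs and 89% with triples, against 97% under independence. With pairs, more than 95% needs about 31% or higher.
- If the Index-to-Index percentage is reported or tested, take the genomic cluster as the independent unit, with each unmatched case as its own cluster, for example through a cluster-robust variance.

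The cost is a few restated figures and one choice of variance. No participants, samples or data are added. The only downside is a less favourable stated precision.

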## Discussion

The World Health Organization (WHO) 2020 Global TB Report showed Indonesia had the second highest TB incidence in absolute numbers [1]. In 2015, the National TB Program budget was estimated to be 133 million US dollars, much of which is unfunded [15]. This study will confirm whether neighbourhoods in the vicinity of routinely diagnosed TB index cases constitute a high-risk sub-population that may warrant active intervention to enhance TB control. Evidence provided will be crucial for the Indonesian TB Control Program in scaling up efforts towards the elimination of TB in a targeted and cost-effective way.

The combination of high precision genotyping, expanded social network questionnaires, and network analyses provides the opportunity to explore *Mtb* transmission. Genomic and social network analyses will provide important information to guide the design of possible interventions that may include active case finding, preventive treatment, and/or enhanced infection control measures in specific locations. For example, if ‘recent’ transmission of *Mtb* from index case households to neighbourhoods is indicated as explaining a large component of high neighbourhood prevalence, an intensive intervention of active case finding for early diagnosis and treatment would be warranted. If transmission ‘hotspots’ within the neighbourhoods can be identified, infection control measures could be considered. If high prevalence and incidence of TB is confirmed but there is a relatively low rate of genomic match within neighbourhoods, it may be that socioeconomic factors that promote reactivation are predominant. An intervention of screening for latent TB infection and initiation of preventive treatment to reduce the possibility of reactivation could be considered, or the focus could be on socioeconomic factors themselves, as suggested by WHO as part of the global strategy to End TB [23].

The proportion of TB cases that can be included in the analysis will be crucial to the ability to interpret these data. As COVID-19 continues to be prevalent in Indonesia, it is possible that recruitment and follow-up will be hindered with fewer than expected numbers being included in the study. This information will be closely monitored and every attempt made to follow-up participants through regular phone contact.

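### The genomic sample-size paragraph compares Index cases matching any of 249 others (at most 10%) with designated Index–contact pairs (60%), so its community comparator is on the wrong scale and is not the planned pair-level analysis

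*Protocol article*

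**What the plan says.** The protocol article treats genomic relatedness in three places.

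- *Sample size, Genomic relatedness*. The community figure is a proportion of cases, the household figure a proportion of pairs, and one sentence joins them: "We expect a maximum of 10% (95% CI 6.3–13.7%) of 250 community diagnosed Index TB cases" will have an isolate identical "to another Index case, compared to approximately 60% of Index TB case/household contact TB case pairs". For neighbourhoods, "Percentages for Index case/neighbourhood case pairs will lie between these values". The numbers of contact cases are given by "Assuming we identify 35 culture-positive cases in contacts in 250 households and 75 culture-positive cases in neighbourhoods". The paragraph claims more than 95% power for community versus household pairs and for community versus neighbourhood pairs. It claims over 80% for household versus neighbourhood pairs at 60% or more against "30% or less of Index case/neighbourhood case pairs are genomically" identical.
- *2) Whole-genome sequencing and social network analysis*. The analysis described compares the odds of relatedness among "pairs within the household, pairs within the neighbourhood, and pairs from different neighbourhoods". The unit is a pair in all three groups.
- *Discussion*. The match rate feeds the interpretation: if prevalence and incidence are high but "there is a relatively low rate of genomic match within neighbourhoods, it may be that socioeconomic factors that promote reactivation are predominant".

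**The concern.** An Index case counts as matched in the community group if it is identical to any one of 249 other Index isolates. A household or neighbourhood pair counts as matched only if one contact isolate is identical to one named Index isolate. With 249 chances against one, the first percentage is far larger than the second at the same underlying relatedness. It also depends on how many Index isolates are sequenced, whereas the expected pair percentages do not.

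The sample-size paragraph nevertheless puts all three groups on one scale, and makes 10% both the comparator and the lower bound for neighbourhood pairs. What is at stake is the community versus neighbourhood contrast. If it were run as that paragraph describes, a neighbourhood pair rate well above background could look no different from the community and neighbourhood transmission could be missed.

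**Working it through.** **Inputs** (all from the genomic sample-size paragraph): community 10% of 250 Index cases; household 60% of 35 pairs; neighbourhood 30% of 75 pairs; alpha 0.05. Two assumptions are needed. The test is taken as two-sided, since the paragraph does not say. The 30% is borrowed from the household versus neighbourhood sentence, since no neighbourhood rate is given for the community contrast.

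**1. Reproducing the plan's figures.**

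Confidence interval: 0.10 ± 1.96 × √(0.10 × 0.90/250) = 6.3% to 13.7%, as stated.

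Power for two independent proportions: Φ[(|p1 − p2| − 1.96 × SE0)/SE1], with SE0 from the pooled proportion and SE1 from the separate ones.

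- Community 10% (250) versus neighbourhood 30% (75): pooled proportion (25 + 22.5)/325 = 0.146, SE0 = 0.0465, SE1 = 0.0562. Φ[(0.20 − 0.0912)/0.0562] = Φ(1.94) = 97.4%. Other versions give 96.3% (continuity-corrected), 97.4% (Fisher) and 94.5% (unpooled).
- Community 10% (250) versus household 60% (35): above 99.9%.
- Household 60% (35) versus neighbourhood 30% (75): 85.5% pooled, 80.0% continuity-corrected, 81.9% Fisher.

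So the stated powers are what one obtains by treating 10%, 30% and 60% as the same quantity in independent samples. Against 10%, the pooled power is 62% at a neighbourhood rate of 20%, 94.9% at 28% and 96.3% at 29%. The claim of more than 95% therefore holds only from roughly 28–29% upwards.

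**2. Converting the 10% to a pair scale.**

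- Index–Index pairs: 250 × 249/2 = 31,125.
- Matching cases: 10% of 250 = 25.
- If they match in twos: 12.5/31,125 = 0.04%.
- If matches are independent: 1 − 0.9^(1/249) = 0.000423, also 0.04%, or about 13 pairs.
- If all 25 form one cluster: (25 × 24/2)/31,125 = 300/31,125 = 0.96%.

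The per-pair community rate implied by 10% is thus about 0.04% to 0.96%. A neighbourhood pair rate of 10% is 10/0.96 ≈ 10 to 10/0.04 ≈ 250 times that background, yet equals the stated comparator.

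**3. Dependence on the number of isolates.** Holding the per-pair probability at 0.000423 and assuming independence, any-match = 1 − (1 − 0.000423)^(n − 1):

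| Index isolates sequenced | Any-match |
|---|---|
| 50 | 2.1% |
| 125 | 5.1% |
| 250 | 10% |
| 500 | 19.0% |

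**4. Power with a per-pair comparator.** Take 0.04% to 0.96% as the community rate and keep 250 as a nominal group size. Power is above 99.9% against 60% (35 pairs) and against 30% (75 pairs). Against a neighbourhood rate of 10% (75 pairs) it is about 90% to 96%, whereas against the stated 10% there is no difference to detect. These are rough figures: pairs share isolates, so 250 is not a true sample size.

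**The case against.** The case on the other side is substantial, and much of it stands.

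- The sequencing section already has a pair-level community group, the pairs from different neighbourhoods. If only that analysis is run, a 10% neighbourhood rate is set against the right background. This stands, and it confines the defect to the sample-size paragraph and to any reading against its values.
- The power figures reproduce and rise after correction, the household versus neighbourhood contrast is pair against pair, and the 10% is given as a maximum. All true. A reader might infer that the study is underpowered or that its numbers must change; the calculations show the opposite.
- Nothing makes 10% a decision threshold. The Discussion gives no number for a low match rate and hedges its conclusion. A reader might infer that the study will wrongly conclude reactivation and choose the wrong intervention; the document does not support that.
- A factor of 250 is only the matched-in-twos end. Under complete clustering the factor is about 10, so only the range can be claimed.
- The plan sets 250 Index cases, so growth with sample size may seem academic. This stands only in part: sequencing needs a cultured isolate, and the Discussion itself warns that recruitment may fall short. A shortfall would lower the community percentage with no change in transmission.

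What the objection does not remove is that the sample-size paragraph itself names the community versus neighbourhood comparison in percent identical, and claims power for it, with different units on the two sides.

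**Conclusion.** The point holds as an error of scale in the genomic sample-size paragraph and an inconsistency with the pair-level analysis in the sequencing section. The 10% is a case-level any-match proportion. Its per-pair equivalent is about 0.04% (matches in twos, or independent matches) to 0.96% (one cluster of 25), taking the stated ceiling at face value. The lower bound set for neighbourhood pairs is therefore too high by a factor of about 10 to 250, and a comparison run as that paragraph describes would tend to miss neighbourhood transmission. The sample size is not undermined. The text should be corrected because the community versus neighbourhood contrast is one of the questions the genomic component is meant to answer.

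**What to change.** 1. State the community comparator per pair, as pairs from different neighbourhoods, so that the sample-size paragraph and the sequencing section describe the same contrast.
2. Remove 10% as comparator and as lower bound for neighbourhood pairs. Keep any-match among Index cases only as a descriptive clustering proportion, reported with the number of isolates sequenced.
3. Restate the power for the pair-level contrasts. Give the neighbourhood rate assumed and the per-pair background assumed, with a range such as 0.04% to 1%.
4. Allow for isolates shared across pairs. One way is a permutation test that compares each contact case's match to its own Index case with its matches to Index cases in other neighbourhoods.

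If any-match is preferred as the measure, use it in every group with equal numbers of candidate partners.

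The cost is rewording one paragraph and a little more analysis work. No new data and no change in recruitment are needed.

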### Outcome measures and statistical analysis

We will categorize TB for Index and household/neighbourhood contacts into four categories: definite TB, probable TB, possible TB, and not TB. Subjects are categorised as definite TB if their *Mtb* culture or Xpert MTB/RIF positive; probable TB if they have TB symptoms, chest x-ray suggestive of TB, and AFB smear-positive but culture negative/not done; possible TB if they have TB symptoms and/or chest x-ray suggestive of TB but all bacteriology examinations negative/not done; and not TB if there was no evidence of TB on a symptom review or investigations. Chest x-rays will be classified as normal, suggestive active TB, suggestive inactive TB, or abnormal not TB based on the radiology report.

The key outcomes of this study are to estimate the TB prevalence and incidence in neighbourhoods around known TB cases, compared to households of known TB cases. TB prevalence defined as the number, percent and 95% confidence intervals (CI) of positive TB cases, according to each TB definition (definite, probable, possible), will be estimated. These proportions will be compared between households, neighbourhoods, and estimates from the Indonesian National Prevalence Survey for Java/Bali. TB incidence defined as incidence rates and 95% CI of positive TB cases according to each TB definition (definite, probable, possible), will be calculated per 1000 person-days. Person-days will be calculated as the days from the date of baseline examination to either: a) the date of TB diagnosis, b) date of death (if died) as reported by household member, c) date of 12-month follow-up examination, or d) date left the neighbourhood area for any household member who has left the area before the 12-month follow-up.

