*Data collection and screening algorithm*. For each Index case, socio-demographic information and results from their Acid-fast bacilli (AFB) smear and/or Xpert MTB/RIF testing at the CHC or hospital will be obtained. Sputum samples will be sent to the research laboratory for culture and storage. From each consenting household contact a symptom screen will be undertaken (Fig 2) as well as enquiry about any history of TB, whether they are on any TB preventive therapy, have any other immunocompromised medical condition, and their socio-demographic information (age, gender, ethnicity, smoking status). The location of each household will be recorded using an electronic geographic coordinate system. Any person with symptoms suggestive of TB (weight loss, night sweats, fever, chest discomfort or pain) will undergo clinical assessment. Any person with a productive cough of any duration will be asked to provide two sputum samples for AFB smear and/or Xpert MTB/RIF testing, and *Mtb* culture [17, 18]. All participants will be offered a chest x-ray, followed by sputum examination if the x-ray has changes suggestive of TB. Chest x-ray reports will be read by a radiologist. Cases with a radiology report showing indication of TB without bacteriology positivity will be consulted to an infectious disease specialist to determine whether they should receive TB treatment or not. All diagnostic procedures and treatment for any person found to have TB will be undertaken according to National TB guidelines.

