### Sample size

#### Prevalence in neighbourhoods

The community estimate of TB prevalence from the Indonesian National Prevalence Survey result for Java was 0.5% (95% CI 0.4 to 0.6%) [22]. We expect a higher rate among TB neighbourhoods, and pragmatically (to justify a policy change), a prevalence of approximately 1.25% culture positive TB cases will be needed in the neighbourhoods. With 4500 neighbourhood participants, the 95% confidence interval around 1.25% will be 0.9 to 1.6%, comfortably above the community estimate.

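### Sputum that was due but never obtained is classed with negative sputum, so definite-TB prevalence is biased downward by an amount the plan cannot show

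*Protocol article*

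**What the plan says.** The Outcome measures and statistical analysis section grades diagnostic certainty in four classes. For the top class, "Subjects are categorised as definite TB if their *Mtb* culture or Xpert MTB/RIF positive". The probable class needs symptoms, a suggestive x-ray and "AFB smear-positive but culture negative/not done". The third class reads "possible TB if they have TB symptoms and/or chest x-ray suggestive of TB but all bacteriology examinations negative/not done". The number, percent and 95% CI are then reported by definition and compared between households, neighbourhoods and the national survey. No denominator is stated.

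The data collection paragraph of the prospective cohort section says when sputum is due. There are two routes: "Any person with a productive cough of any duration will be asked to provide two sputum samples", and "All participants will be offered a chest x-ray, followed by sputum examination if the x-ray has changes suggestive of TB". Other symptoms lead elsewhere: "Any person with symptoms suggestive of TB (weight loss, night sweats, fever, chest discomfort or pain) will undergo clinical assessment".

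The sample size section on neighbourhood prevalence gives a survey estimate for Java of 0.5% (95% CI 0.4 to 0.6%). It says that, for a policy change, "a prevalence of approximately 1.25% culture positive TB cases will be needed in the neighbourhoods", and it computes precision on 4500 neighbourhood participants.

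**The concern.** A person who tested negative and a person who was never tested carry different information about definite TB, yet the definitions give them the same label. Dividing the definite cases by all participants then treats every untested person as bacteriologically negative. Those whose sputum was due have already screened positive by cough or x-ray, so confirmed cases should be concentrated among them. The x-ray route does not require a productive cough, so some people on it may be unable to give a specimen.

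Two readings of the result are at stake. One is whether confirmed prevalence in neighbourhoods reaches the level that the plan ties to a policy change. The other is the household-neighbourhood comparison, which is a key outcome. Household contacts live with the Index case, while neighbours are not told who that is, so willingness to provide sputum could differ between the groups.

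**Working it through.** **Inputs.** From the sample size section: prevalence p = 1.25%, n = 4500, stated 95% CI 0.9 to 1.6%, community estimate 0.5% (0.4 to 0.6%). The documents give no sputum completion rate, so every value of m below is an assumption. Here m is the share of true bacteriologically positive people whose due sputum was never obtained.

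**1. The plan's own interval.** Wald: p ± 1.96 × √(p(1 − p)/n) = 0.0125 ± 1.96 × √(0.0125 × 0.9875/4500), which gives 0.925% to 1.575%. This agrees with the stated 0.9 to 1.6% (Wilson 0.96 to 1.62%, exact 0.94 to 1.61%). The calculation takes bacteriology as complete in all 4500.

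**2. Unobtained sputum counted as not definite.** Everyone stays in the denominator, so observed prevalence = 1.25% × (1 − m). The last column is 1.25%/(1 − m).

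| m (assumed) | Cases counted of 56.25 | Observed (95% CI) | True prevalence needed to observe 1.25% |
|---|---|---|---|
| 0 | 56.2 | 1.25% (0.93–1.57) | 1.25% |
| 10% | 50.6 | 1.13% (0.82–1.43) | 1.39% |
| 20% | 45.0 | 1.00% (0.71–1.29) | 1.56% |
| 30% | 39.4 | 0.88% (0.60–1.15) | 1.79% |

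The upper limit falls below 1.25% at m of about 23%. The lower limit reaches 0.6% at m of about 30% and 0.5% at about 40%.

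**3. If untested people differ from tested ones.** Let k be the share of sputum-eligible people without a result, and r the positivity of the untested relative to the tested. Then observed prevalence = 1.25% × (1 − k)/((1 − k) + r × k).

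- r = 0: 1.25% throughout, so no bias.
- r = 0.5: 1.18%, 1.11% and 1.03% at k = 10%, 20% and 30%.
- r = 1: 1.13%, 1.00% and 0.88%, as in step 2.
- r = 2: 1.02%, 0.83% and 0.67%.

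The direction is the same for every r above 0. The size depends strongly on r.

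**4. Household-neighbourhood comparison.** With equal true prevalence, the observed ratio equals the ratio of the shares of true positives with a result. Purely as an illustration, 95% in households against 75% in neighbourhoods gives 0.95/0.75 = 1.27. The documents support neither figure.

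**The case against.** The strongest reply is that these classes grade certainty. An untested person is, by definition, not a confirmed case, and a confirmed-case prevalence reported beside wider classes can be read as a minimum. Denominators and missing-data methods may also sit in an analysis plan that is not shown. Part of this stands: the denominator is inferred from the 4500. The pooling itself, however, is written into the definitions, and the minimum is nowhere labelled as one.

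Some stronger readings are tempting, but the documents do not support them.

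- *Untested people are treated as free of TB.* They are not. They appear under possible TB, or under probable TB if smear-positive without a culture or Xpert result, and suggestive x-rays without positive bacteriology go to a specialist. Only the definite estimate loses them.
- *Everyone not tested is a missed test.* The same label covers people with, say, fever or weight loss but no productive cough or suggestive x-ray, for whom sputum is not stated to be due.
- *Substantial missing sputum is built into the design, and more so in neighbours.* No completion rate is given, overall or by group. The screening figure is not shown, and monthly completeness checks are planned.
- *A stated part of the 0.75-point excess (1.25% − 0.5%) would be lost.* That assumes the survey's 0.5% is free of the same problem. If the survey also counted missing sputum as negative, correcting only this study would bias the contrast upward.
- *The study would miss its decision threshold.* The 1.25% is an approximate planning value for culture-positive TB. Definite TB also admits Xpert positives, which could offset part of a shortfall. With 20% missing, the lower limit of 0.71% is still above the survey's upper limit of 0.6%.

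**Conclusion.** The point holds in a limited form and is worth correcting. With all participants in the denominator, an unobtained due sputum can remove a person from the definite-TB count but never add one. The bias is therefore downward, and it is zero only if no case is missed. Its size cannot be found from the documents. The fall from 1.25% to between 1.13% and 0.88% rests on an assumed 10% to 30% of true positives without a result. Distortion of the household-neighbourhood comparison is conditional on differing completion. Nothing can be concluded about the bias in the contrast with 0.5% until the survey's handling of missing sputum is known.

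**What to change.** In the Outcome measures and statistical analysis section:

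- Classify each person's bacteriology as positive, negative, due but not obtained, or not due, and keep these apart within the possible and probable classes.
- State the denominator, and report sputum completion separately for households and neighbourhoods.
- Report the crude definite-TB proportion, labelled a lower bound. Beside it, give an estimate by multiple imputation or inverse-probability weighting among the sputum-eligible, using group, symptoms, x-ray class, age, gender and TB history, all of which are already collected.
- Add a sensitivity range for departure from missing at random, for example over values of r as in step 3 of the working.
- Use both estimates when reading the result against 1.25% and between groups. Compare with the survey only on the same handling of missing sputum.

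The cost is wording and some analysis time, with no extra visits, staff or specimens. The adjusted estimate relies on missing at random among screen-positive people. That is open to doubt if inability to produce sputum is related to being positive, which is why it should not replace the crude figure. The model would rest on few events (about 56 expected neighbourhood cases at 1.25%), and the interval would be slightly wider.
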